### Secondary hypotheses

H2: An integrated intervention of exercise and PCST will be more efficacious in improving pain and self-reported physical function than either PCST or exercise alone at 32 weeks and 52 weeks.

H3: An integrated intervention will be more efficacious in improving psychological function, functional performance, quality of life, physical activity levels and perceived response to treatment than either PCST or exercise alone immediately following the intervention and at 32 weeks and 52 weeks.

H4: Exercise will lead to greater improvements in muscle strength than PCST; PCST will lead to greater improvements in psychological parameters than exercise; and an integrated intervention will lead to greater improvements in both strength and psychological parameters at measured time points.

H5: Adherence to exercise during the 9-month unsupervised follow-up period will be greater with an integrated intervention than with an intervention of exercise alone.

H6: An integrated intervention will be more cost-effective than an intervention of exercise or PCST alone when costs are compared and related to the effects of the intervention at 52 weeks.

H7: Specific patient baseline characteristics will moderate or predict treatment effects while pre- to post-treatment changes in the targeted cognitions, behaviours and physical impairments will mediate the effects of PCST and exercise on subsequent patient pain and disability.

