#### *Integrated exercise and PCST intervention*

This intervention will integrate both the exercise and PCST programs described above within a single integrated treatment session. While the therapist will deliver the same PCST program, examples relating to exercise and activity can be used as material for the skills being taught to a greater extent than in the PCST alone group. Participants will be encouraged to incorporate the learned PCST skills into their home exercise program and specific training will be provided on how learned skills can be applied during the exercise performance at the same clinic visit. Each physiotherapy treatment session will be 70 min in length which includes 25 mins of exercise and 45 mins of PCST (Figure 1, Table 2).

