### Economic evaluation

The economic evaluation will assess the incremental cost of the integrated intervention compared with PCST and with exercise. In each case the incremental cost will be compared to the incremental benefits of treatment in terms of a clinically significant improvement in pain, a clinically significant improvement in function, and the difference in quality adjusted life years (QALYs). The incremental QALYs will be measured by the between group difference in the mean AQoL score over 12 months. A social perspective on costs will be taken and will include resource use incurred both by health services and by the participant irrespective of payment source. Health care costs will be calculated from the utilisation data and average unit costs for each item. We will not include the costs of training the physiotherapists in the delivery of PCST in the primary analysis. The inclusion of time/productivity gains is controversial and the cost effectiveness ratios will be calculated with and without these “indirect costs”. Confidence intervals for incremental cost effectiveness will be calculated directly using non parametric bootstrapping. In addition we will calculate a cost effectiveness acceptability curve based for a range of hypothetical money values of outcomes [76]. This will be done using individual cost and outcome data over the 12 months or, if adjustments for imbalance at baseline and clustering of patients by physiotherapist are necessary, analysed using a mixed linear regression model [77].

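### Bootstrap intervals taken directly on the cost-effectiveness ratio can be uninterpretable if the effect difference between the active arms is not clearly above zero; net-benefit intervals from the same replicates would avoid this (minor)

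*Protocol article*

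**What the plan says.** Under Economic evaluation, the integrated arm is compared with PCST and with exercise. In each comparison the extra cost is set against three effects: responder outcomes for pain and for function, and QALYs. On QALYs the protocol says "The incremental QALYs will be measured by the between group difference in the mean AQoL score over 12 months". Ratios are the named summary: "the cost effectiveness ratios will be calculated with and without these “indirect costs". On uncertainty it says "Confidence intervals for incremental cost effectiveness will be calculated directly using non parametric bootstrapping", and the next sentence adds "In addition we will calculate a cost effectiveness acceptability curve based for a range of hypothetical money values of outcomes". A regression alternative is kept in reserve: "if adjustments for imbalance at baseline and clustering of patients by physiotherapist are necessary, analysed using a mixed linear regression model".

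The hypothesis served is H6, under Secondary hypotheses: "An integrated intervention will be more cost-effective than an intervention of exercise or PCST alone", assessed at 52 weeks. The section gives no expected difference, SD or cost figure for any economic outcome. It does not say what happens to replicates whose effect difference is zero or negative.

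**The concern.** A cost-effectiveness ratio (ICER) carries a clear meaning only while its denominator keeps one sign. Take an extra cost of 500 money units as an illustration. A replicate that costs 500 more and loses 0.01 QALY gives 500/(−0.01) = −50,000. A replicate that saves 500 and gains 0.01 QALY gives −500/0.01 = −50,000. The first is the worst possible outcome and the second the best, yet the ratio is the same. A replicate that costs 500 more and gains 0.01 gives +50,000. Ranked by ratio, the dominated replicate therefore falls below an ordinary positive one and looks better than it.

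A negative lower limit could then be read as possible cost saving when it comes from replicates in which the integrated program costs more and does worse. At stake is how the H6 results are read. The clinical primary analysis is not touched.

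**Working it through.** **1. Number of patients behind the estimates.** The protocol's Sample size section gives SDs and target differences that correspond to d = 0.5 (function) and 0.6 (pain), a pre-post correlation of 0.50, 80% power and a two-sided 5% level.
- Per arm: 2 × (1.96 + 0.842)² × (1 − 0.5²)/d². This is 47.1, so 48, for function, and 32.7, so 33, for pain.
- Clustering: 48 × 1.30 = 62.4, so 63. Dropout: 63/0.9 = 70.

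The protocol's figures reproduce. I use 63 per arm with 52-week data.

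**2. How often replicates fall below zero effect.** The remaining inputs are assumptions, because the protocol gives none: AQoL SD 0.15 to 0.20, true QALY gain 0.02 to 0.05, responder proportion 50% in the comparator. Clustering is ignored.

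Let k be the true effect difference divided by its standard error. For QALYs, SE = SD × √(2/63), that is 0.0267 or 0.0356. For responders, SE = √[p₁(1−p₁)/63 + p₂(1−p₂)/63]. In SE units the trial estimate is N(k, 1) and each replicate is N(estimate, 1). So:
- average share of replicates below zero effect = Φ(−k/√2);
- share of trials with more than 2.5% of replicates below zero effect = Φ(1.96 − k).

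| Assumed effect | k | Replicates below zero | Trials with more than 2.5% below zero |
|---|---|---|---|
| QALY gain 0.02, SD 0.20 | 0.56 | 35% | 92% |
| QALY gain 0.02, SD 0.15 | 0.75 | 30% | 89% |
| QALY gain 0.05, SD 0.20 | 1.40 | 16% | 71% |
| QALY gain 0.05, SD 0.15 | 1.87 | 9% | 54% |
| Responders 60% v 50% | 1.13 | 21% | 80% |
| Responders 65% v 50% | 1.72 | 11% | 59% |
| Responders 70% v 50% | 2.34 | 5% | 35% |

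Where extra cost is clearly positive, the last column is also the share of trials whose percentile ratio interval has a negative lower limit.

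**3. What the negative ratios consist of.** This depends on the cost difference. Assume a mean extra cost of 500.
- Cost SD 600: SE = 600 × √(2/63) = 106.9, so the cost difference is 4.7 SE. On average Φ(−4.68/√2) = 0.05% of replicates have lower cost. Practically all negative ratios are then dominated replicates.
- Cost SD 1500: SE = 267.3, so 1.87 SE. On average Φ(−1.87/√2) = 9% of replicates have lower cost, and the two kinds can mix.

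**4. Coverage and mixing.** These come from a simulation on standardised normal differences, with cost and effect independent, 1,500 trials of 2,000 replicates per setting, true effect 0.25 to 4 SE and cost difference 0.5 to 5 SE.
- The simple percentile interval of the ratio covered 87% to 99%. It fell to 87–89% only at an effect of 0.25 SE with a cost difference of 2 to 5 SE; elsewhere it was 94.5% to 98.9%.
- The net-benefit interval, evaluated at the true ratio, covered 94% to 97%.
- More than 2.5% of replicates lay in both the dominated and the cost-saving quadrant in 65–73% of trials (cost 0.5 SE, effect 0.25 to 1 SE), 32–34% (cost 2 SE, same effects), 0–0.3% (cost 5 SE) and about 1% or less (effect 4 SE).

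**The case against.** The strongest reply has four parts.

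First, the article does not say that limits are percentiles of the ranked ratio. Bootstrapping costs and effects is standard, and handling of quadrants is a detail that an article may leave to the full plan. This is partly right. But the section names ratios as the summary and says their uncertainty is bootstrapped directly, and the natural reading is an interval on the ratio. That is a stated choice, though a loosely described one.

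Second, the acceptability curve classifies each replicate by net benefit at each money value, so a dominated result never counts as favourable. This stands, and it is the main reason why the point is minor. The curve comes in addition to the ratio interval, however, and does not replace it. The reserve regression model changes how the differences are estimated, not how a ratio is ordered.

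Third, a reader might infer that dominated and cost-saving results would always be mixed. The protocol does not support that. Mixing needs a cost difference of uncertain sign, and the integrated arm has the longest sessions ("Each physiotherapy treatment session will be 70 min in length which includes 25 mins of exercise and 45 mins of PCST"), so its delivery cost is higher unless offset elsewhere. With a clearly higher cost, mixing disappears, but the negative ratios are then almost all dominated replicates, and the misleading ordering remains.

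Fourth, frequent negative lower limits largely restate that an assumed small QALY gain would not be statistically significant. That is true. The percentages in the table measure how often the ambiguity would arise and are not error rates.

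**Conclusion.** The point holds as one of interpretation. An interval taken directly on the ratio can be uninterpretable here, because between active arms an effect difference of roughly 0.6 to 1.9 SE is plausible for QALYs, and dominated replicates then sit at the end that looks favourable. All economic inputs behind that range are assumptions. For a large responder difference (70% v 50%), only about 5% of replicates fall below zero and the issue is slight.

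Two stronger readings are not supported. A reader might infer that the interval is invalid in the sense of grossly undercovering. Simulated coverage was mostly 95% or more, and was clearly low (87–89%) only when the effect was almost nil. At exactly zero effect the ratio is undefined, and coverage has no meaning. A reader might also infer that H6 stands or falls on the ratio interval. No section ties it to that interval alone, and the acceptability curve will be available beside it. Severity: minor.

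**What to change.** Keep the bootstrap and change what is reported from it. For each comparison and each effect measure, give the 95% interval for incremental net benefit (money value × effect difference − cost difference) at the money values already used for the acceptability curve, and show the replicates on the cost-effectiveness plane. Give the ICER as a point estimate, with a ratio interval only when essentially all replicates lie in one quadrant. One added sentence under Economic evaluation is enough.

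This needs no new data and no further resampling. The small cost is that results appear over a range of money values instead of as a single interval.

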### Timelines

This study has been funded by Australian Health Management and ethics approval was obtained at the University of Melbourne in March 2010 and at the University of Queensland in June 2010. Radiation Safety approval to conduct weight bearing knee joint x-rays was approved at the Universities of Melbourne and Queensland in June 2010. Recruitment and training of the physiotherapists occurred after this time period. The anticipated timelines for the project at both sites are as follows:

August 2010 Baseline testing commences

March 2012 Recruitment complete

June 2012 All participants complete immediate post intervention testing (Week 12)

March 2013 All participants complete 9 month follow-up (Week 52)

## Discussion

Osteoarthritis is a complex chronic disease with many factors that contribute to the pain and disability. This reinforces the need for a biopsychosocial approach when developing treatments aimed at improving the self-management of this disease. Previous studies of muscle strengthening exercises have shown significant improvements in pain, physical function and performance measures [5,25,78]. However, individuals with knee OA also require treatment that addresses the psychological impairments that are commonly found [79]. An individuals’ coping mechanism for how they deal with pain is of crucial importance [80]. For instance, those who develop maladaptive coping behaviours such as limiting activity due to fear of increased joint damage and/or increased pain, avoiding social obligations, pain catastrophising and worry can lead to reports of increased pain and functional decline [80-83]. Depression, anxiety and stress are also significant predictors of upcoming pain symptoms [3,31,84]. Overwhelmingly, the research suggests that pain catastrophising and self-efficacy cognitive variables are important predictors of pain and function [13,29,85]. Keefe et al., provide support for the use of PCST in improving psychological functioning in this patient population [24,34,35,81]. Thus, given that both exercise and PCST have been shown to be effective for symptomatic relief in knee OA, we contend that an integrated PCST and exercise program is likely to be more efficacious than either intervention alone.

The study design has several major strengths. First, considerable attention has been paid to quality control of the PCST intervention. The project physiotherapists will undergo rigorous training and accreditation to deliver the PCST intervention. All sessions will be audio recorded and then reviewed by the site psychologist. Regular meetings will be held throughout the study to provide ongoing practice and supervision for the physiotherapists. PCST treatment fidelity will be formally determined via rating of a random sample of the PCST treatments. Second, the outcome measures used are valid and reliable, cover a range of clinically important constructs and include those recommended for clinical trials of OA [44]. These include self-report measures of pain, function, quality of life and global response to treatment. A range of other measures is also included to encompass functional performance, strength, psychological functioning and physical activity levels. In addition, a health economic assessment is included given the need to justify the cost-effectiveness of treatments in the current economic climate. Third, the study has been designed with attention to methodological features such as randomization, concealed allocation and blinded outcome assessment. The sample size has been calculated to detect minimal clinically important differences between groups, taking into account the clustering effects of the physiotherapists.

## Conclusion

This study uses a randomized controlled trial design to investigate the efficacy of an integrated exercise and PCST program delivered by physiotherapists in improving pain and physical function in those with knee OA compared with exercise or PCST alone. The novel findings will enable evidence-based recommendations as to the efficacy of this conservative option for the management of patients with knee OA.
